### 1.3 SCHEDULE OF ACTIVITIES

| Activity                             | Screening | 0 Month    | 6 Months   | 12 Months  |
|--------------------------------------|-----------|------------|------------|------------|
| Eligibility Assessment               | ✓         |            |            |            |
| Informed Consent                     | ✓         |            |            |            |
| Randomization                        |           | ✓          |            |            |
| Medical Assessment                   |           | ✓          | ✓          | ✓          |
| EQ-5D-5L Quality of Life Assessment  |           | ✓          | ✓          | ✓          |
| Frailty Index Evaluation             |           | ✓          | ✓          | ✓          |
| ADL/IADL Assessment                  |           | ✓          | ✓          | ✓          |
| Healthcare Utilization & Expenditure |           | ✓          | ✓          | ✓          |
| Medication Adherence Monitoring      |           | ✓          | ✓          | ✓          |
| Patient Satisfaction Survey          |           |            | ✓          | ✓          |
| Intervention Delivery (Multi-FrAME)  |           | ✓          | Continuous | Continuous |
| Adverse Event Monitoring             |           | Continuous | Continuous | Continuous |
| Lab Tests & Biomarker Collection     |           | ✓          | ✓          | ✓          |

Interim Analysis

After 50% of 12-months

Final Data Collection & Analysis

✓

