| Decrease healthcare utilization                                                                 | Reduction in healthcare visits and hospital admissions      | Reflects stabilized health conditions                                             | Coordinated care reduces the need for acute services            |
| Decrease healthcare expenditure                                                                 | Reduction in total healthcare costs                         | Economic impact of reduced healthcare spending                                    | Efficient management techniques                                 |

|                               |                                                                |                                            |                                                      |
|-------------------------------|----------------------------------------------------------------|--------------------------------------------|------------------------------------------------------|
| Improve medication adherence  | Increase in Medication Adherence Reporting Scale (MARS) scores | Indicates adherence behavior changes       | Education and psychosocial support improve adherence |
| Increase patient satisfaction | Higher scores in Patient Satisfaction Questionnaires           | Direct feedback on care experience         | Patient-centered care enhances satisfaction          |
| Reduce mortality rates        | Reduction in all-cause mortality over study duration           | Key determinant of long-term effectiveness | Comprehensive care strategies prolong life           |

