## 6.2 ADMINISTRATION AND/OR DOSING

- **Intervention Delivery:** Conducted by trained healthcare professionals at participating PHCs, assisted by trained investigators from the study team.
- **Monthly Contact Sessions:** All testing, data collection, clinical management, physiotherapy, and physical activity reviews conducted during these sessions.
- **Health Diary:** Each participant will receive a "Health Diary," serving multiple purposes:
  - **Intervention Log:** Enables participants and caregivers to maintain a daily record, helping verify intervention fidelity.
  - **Documentation Hub:** A single point for filing lab reports and documenting other medications and health updates during the trial.
  - **Information, Education, and Communication (IEC):** Contains materials for health promotion, behavior change, and education. Participants can refer to these resources for ongoing learning and support.

| Intervention Category               | Specifications                                                                                                                                                           | Dose/Frequency                                                                                                                                                                                                               | Mode of Administration                      | Self-care/Caregiver Required                   |
|-------------------------------------|--------------------------------------------------------------------------------------------------------------------------------------------------------------------------|------------------------------------------------------------------------------------------------------------------------------------------------------------------------------------------------------------------------------|---------------------------------------------|------------------------------------------------|

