**B. Secondary Endpoints:**

i. **Frailty Index:**

- a. **Tool:** Cumulative Deficit Frailty Index (Rockwood et al., 2005)
- b. **Details of the index:** The study will employ a deficit-based frailty index (FI) to assess frailty status, following the cumulative deficit model (Ghosh et al., 2023). The FI will be constructed using 40 health-related variables covering multiple domains, including chronic diseases, functional limitations, cognitive impairments, and self-perceived health status. Each variable will be coded as 0 (deficit absent), 1 (deficit present), or assigned an intermediate value (e.g., 0.5) for partial deficits. The FI score for each participant will be calculated by dividing the total number of deficits present by the total number of variables assessed, resulting in a score ranging from 0 to 1. Based on this score, participants will be categorized as robust ( $FI \leq 0.15$ ), prefrail ( $FI > 0.15$  to  $\leq 0.24$ ), or frail ( $FI > 0.25$ ). This method provides a comprehensive and standardized approach to measuring frailty by accounting for the accumulation of health deficits across multiple domains.
- c. **Assessment Schedule:** Assessed at baseline, 6, and 12 months.

ii. **ADL/IADL:**

- a. **Tool:** Lawton and Brody Instrumental Activities of Daily Living Scale (Lawton & Brody, 1969)
- b. **Assessment Schedule:** Conducted at baseline, 6, and 12 months.

iii. **Healthcare Utilization:**

- a. **Tool:** Custom questionnaire capturing healthcare visits and hospital admissions.
  - b. **Data Collection:** Monthly via participant health diaries and healthcare records.
- iv. **Healthcare Expenditure:**
  - a. **Assessment:** Monthly data collection from participant reports and receipt submissions.
- v. **Medication Adherence:**
  - a. **Tool:** Medication Adherence Reporting Scale (MARS) (Thompson et al., 2000)
  - b. **Frequency:** Assessed at 0, 6, and 12 months.
- vi. **Patient Satisfaction:**
  - a. **Tool:** Patient Satisfaction Questionnaire (Greenfield & Attkisson, 1989)
  - b. **Frequency:** Evaluated at 6, and 12 months.
- vii. **Mortality Rates:**
  - a. **Data Collection:** Continuous monitoring throughout the study period using health records and family reports.

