#### 12.4.3 ANALYSIS OF THE SECONDARY ENDPOINT(S)

- **Outcomes:** Frailty progression, ADL/IADL scores, healthcare utilization, costs, patient satisfaction, medication adherence, mortality, along with all the laboratory measurements.
- **Method:** Each secondary outcome will be clearly defined and analyzed to evaluate the broader impacts of the intervention on participants' health and well-being. Frailty progression will be assessed through a frailty score as a continuous measure. Functional limitations will include work-limiting conditions, mobility, Activities of Daily Living (ADL), and Instrumental Activities of Daily Living (IADL), scored on an ordinal scale, using categorical measures (e.g., "able" vs. "unable"). Health care utilization will be measured by tracking healthcare events (e.g., visits, hospitalizations) in a binary or categorical format, while health care expenditure will be recorded as a continuous variable, capturing both mean and median expenditures. Medical adherence will be represented as a percentage, indicating the proportion of prescribed medications participants adhered to. Statistical comparisons of these secondary outcomes between the intervention and control groups will employ appropriate tests for each outcome variable type to assess differences. Mixed-effect models will calculate adjusted odds ratios to determine effect sizes, with corresponding confidence intervals to quantify the intervention's impact.

---

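### Medication adherence is defined and measured as a MARS score, but section 12.4.3 analyses a percentage of prescribed medicines that has no stated source and no link to MARS

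*Protocol*

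**What the plan says.** Section 3 (objectives table, secondary objectives) gives the endpoint for improving medication adherence as "Increase in Medication Adherence Reporting Scale (MARS) scores".

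Section 9.1, part B, item v lists MARS as the tool, with no second instrument, and gives the frequency as "Assessed at 0, 6, and 12 months". The Schedule of Activities in section 1.3 has a row "Medication Adherence Monitoring" ticked at the same three times.

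Section 12.4.3 keeps medication adherence in its list of secondary outcomes but describes the analysis variable differently: "Medical adherence will be represented as a percentage, indicating the proportion of prescribed medications participants adhered to". It does not mention MARS. For the secondary outcomes as a group it adds: "Mixed-effect models will calculate adjusted odds ratios to determine effect sizes".

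**The concern.** A scale score and a share of prescribed medicines are different quantities. Each needs its own data and its own model. Sections 3 and 9.1 commit the trial to the first, and section 12.4.3 commits it to the second.

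Two consequences follow if nobody reconciles them. The MARS data would be collected at three visits with no stated analysis, while the stated analysis would call for data that no section arranges to collect. The choice between the two could also be left until results are visible, which opens a listed secondary objective to selective reporting.

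The variable itself is in dispute. The general promise in 12.4.3 to use tests suited to each outcome type therefore does not settle the matter.

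**Working it through.** No arithmetic applies, because the protocol states no figure for this endpoint. The check sets the relevant places side by side.

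1. **Definition.** Section 3: a rise in MARS score.
2. **Instrument.** Section 9.1 B.v: MARS only.
3. **Timing.** Sections 9.1 and 1.3: 0, 6 and 12 months, so a baseline value is expected.
4. **Analysis variable.** Section 12.4.3: the share of prescribed medicines to which the participant adhered, as a percentage.
5. **Link from 2 to 4.** None. The protocol refers to MARS only as producing scores. It gives no conversion to a percentage, and no numerator, denominator or recall period for one.
6. **Another source for 4.** No pill count, refill record or other count of prescribed against taken medicines is scheduled. The list of case report forms in section 15 shows medication adherence on the follow-up form at 6 and 12 months, without saying in what form.

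The one remaining candidate is the health diary:

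- Section 6.2 describes it as an intervention log that helps verify fidelity, and as a place to document other medicines. It describes no count of prescribed against taken.
- The intervention table in section 6.2 puts a diary for improving adherence inside the medical management component.
- Section 6.3 issues it together with the daily intervention, to record intake or practice of that intervention.
- No section names it as the source for the adherence endpoint.
- A diary handed out during the trial would not obviously supply the month-0 value that sections 1.3 and 9.1 require.

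Using the diary would also mean measuring adherence with something that is itself meant to raise adherence.

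Result: the definition, instrument and timing agree with one another. The analysis variable agrees with none of them, and nothing in the document connects it to a data source.

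**The case against.** The strongest reply is that this is loose wording. MARS is still scheduled at all three visits, medication adherence is still on the outcome list in 12.4.3, and the data survive to be analysed properly. The annexed case report forms and diary are not shown and may contain more detail. This stands as a limit on the harm: nothing is irretrievably lost, and the wording can be reconciled before analysis. It does not remove the contradiction between sections 3 and 9.1 on one side and 12.4.3 on the other.

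Four stronger readings are tempting, and the document does not support them.

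- **That MARS cannot yield such a percentage.** The protocol does not reproduce the MARS items or scoring. What can be said is that no conversion is stated.
- **That there would be no control-arm data.** Section 6.2 says "Each participant will receive a 'Health Diary,' serving multiple purposes", section 9.3 has participants keeping daily logs without limiting this to one arm, and section 9.1 uses diaries as a source for healthcare utilization, which is compared between arms. The intervention table and section 6.3 point the other way. Control-arm diaries are unclear, not absent.
- **That an odds ratio cannot fit this outcome.** A count of medicines adhered to out of those prescribed can go into a binomial mixed model, and an ordinal score into a cumulative-odds mixed model. Both give an odds ratio without any cut-off.
- **That information will be lost by dichotomising.** Section 12.4.3 does not say that adherence will be dichotomised, so no loss of efficiency can be charged to the plan.

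The odds-ratio sentence covers all secondary outcomes. It matters here only because it would conflict with a mean difference once the analysis variable is corrected.

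**Conclusion.** The point holds as a contradiction in the definition of one secondary endpoint. The adherence measure that sections 3 and 9.1 fix is not the one that 12.4.3 analyses, and the one in 12.4.3 has no specified instrument, denominator or time window.

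It affects one of the seven secondary endpoints numbered in section 9.1. The primary endpoint, its analysis and the sample size are untouched. It should be corrected before any between-arm comparison is seen.

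The conclusion rests on the protocol text alone. An annexure could show how the percentage was meant to be obtained, but sections 3 and 9.1 would still name a different endpoint from 12.4.3.

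**What to change.** In section 12.4.3, replace the percentage sentence with:

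*Medication adherence is the MARS total score at 6 and 12 months, compared between arms with a linear mixed model with random effects for PHC and participant, adjusted for baseline MARS, and reported as a mean difference with 95% CI.*

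The participant effect is needed because both follow-up scores enter one model. The PHC effect alone would ignore the correlation between two scores from the same person.

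Then exempt this endpoint from the odds-ratio sentence that follows. Otherwise the two sentences would name different effect measures for the same outcome.

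Any intake percentage taken from the diary should be a descriptive measure of fidelity only.

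An alternative is to keep the percentage as the endpoint. That would mean changing sections 3 and 9.1, defining its source, denominator and time window, and collecting it in the same way in both arms at 0, 6 and 12 months. It is a legitimate repair but a dearer one. The MARS route costs one or two sentences and uses data already scheduled.

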#### 12.4.4 SAFETY ANALYSES:

Frequency and severity comparisons across groups in terms of AE and SAE reported and other details from documentation in safety reports.

---

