## 2.3 RISK BENEFIT ASSESSMENT

### 2.3.1 KNOWN POTENTIAL RISKS:

#### A. Nutritional Supplementation

##### i. Vitamin D3 (Cholecalciferol)

- **Hypercalcemia:** Excessive intake can lead to elevated calcium levels, causing nausea, vomiting, weakness, frequent urination, and kidney damage. Symptoms may appear when serum calcium exceeds 10.5 mg/dL (Jones, 2008).
- **Hypervitaminosis D:** Chronic high doses can result in toxicity, symptoms include confusion, disorientation, and cardiovascular complications (Holick, 2007).
- **Gastrointestinal Disturbances:** Constipation, diarrhea, or abdominal discomfort may occur (Vieth, 1999).

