#### iii. **Liver and Kidney Function Tests:**

- a. **Outcome Measurement:** Changes in enzyme levels (e.g., ALT, AST) and creatinine (along with eGFR).
  - b. **Justification:** Indicates improvements in organ function.
- iv. **Complete Blood Count (CBC):**
  - a. **Outcome Measurement:** Hemoglobin and hematocrit levels. Along with WBC ratios.
  - b. **Justification:** Indicates overall hematological health and potential for anemia improvement.
- v. **Micronutrient Levels:**
  - a. **Outcome Measurement:** Changes in Vitamin D, iron, and calcium levels.
  - b. **Justification:** Provides insight into nutritional and bone health improvements.
- vi. **Thyroid Function Tests:**
  - a. **Outcome Measurement:** Changes in TSH, T3, and T4 levels. Changes in testosterone, oestrogen and progesterone levels
  - b. **Justification:** Reflects endocrine health and potential metabolic improvements.

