| Medical Management                  | Medication review and optimization; Diary for improving adherence and compliance                                                                                         | Monthly, with diary data being updated daily                                                                                                                                                                                 | In-person at PHC                            | Self-care, with caregiver assistance if needed |
| Nutritional Support                 | Vitamin D3, iron, folic acid, calcium, and protein supplements                                                                                                           | Doses are subject to the results of participants' biochemical tests for the respective nutrients. These doses will be monitored and modified as necessary to maintain nutrient levels within the biological reference range. | Oral supplementation                        | Self-care                                      |
| Physiotherapy and Physical Activity | Customized exercise program                                                                                                                                              | Monthly sessions, with daily exercises                                                                                                                                                                                       | In-person sessions and home-based exercises | Self-care, with caregiver support for safety   |
| Psychosocial Support                | Individual and group therapy sessions (Including therapeutic games, storytelling, friendship enrichment program), health promotion through the health diary IEC material | Breathing exercise and Meditation on daily basis, Psychological Counselling as per the patient's requirement, and Group sessions once in 2-3 month                                                                           | In-person or via tele-health                | Self-care                                      |

Details of the intervention are provided as an additional file.

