## 9.2 SAFETY ASSESSMENTS

- **Adverse Events:**
  - **Definition:** Any undesirable experience associated with the use of the intervention.
  - **Assessment Frequency:** Continuous monitoring with mandatory reporting within 24 hours of occurrence.

- **Severity Classification:** Mild, Moderate, Severe based on impact on daily activities.
- **Serious Adverse Events:**
  - **Definition:** Events resulting in death, hospitalization, disability, or jeopardizing participant health.
  - **Reporting:** Immediate notification to Principal Investigator and ethics board, with documentation filed timely.
- **Vital Signs and Routine Checks:**
  - **Parameters:** Blood pressure, heart rate, weight, and BMI.
  - **Frequency:** Monthly during contact sessions.
- **Lab Tests:** (also as outcomes as described above in section 3.2)
  - **Assessment Schedule:** 0, 6, and 12 months.
  - **Tests Included:** (detailed as endpoints in section 3.2)
    - **Biochemical Metrics:** Blood glucose, lipid profile, liver function tests, kidney function tests.
    - **Hematological Metrics:** Complete blood count, hemoglobin levels.
    - **Micronutrient Profiles:** Levels of Vitamin D, iron, and calcium.
    - **Hormonal Profiles:** Thyroid function tests and other relevant hormone levels.

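### Laboratory tests listed as safety assessments are named only in the secondary-endpoint analysis, and section 12.4.4 does not assure that out-of-range values are counted by arm

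*Protocol*

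**What the plan says.** All references are to the Protocol.

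- **Risks (2.3.1, part A).** Hypercalcaemia is listed under both vitamin D3 and calcium. Under vitamin D3 it is linked to kidney damage and given a figure: "Symptoms may appear when serum calcium exceeds 10.5 mg/dL". Vitamin D toxicity and iron overload with organ damage are also listed.
- **Target (6.2, Nutritional Support).** Supplement doses depend on biochemical results and are "modified as necessary to maintain nutrient levels within the biological reference range".
- **Collection (9.2, Safety Assessments).** Laboratory tests at 0, 6 and 12 months include liver and kidney function and "Levels of Vitamin D, iron, and calcium". A note says that they serve "also as outcomes as described above in section 3.2".
- **Outcome definition (3.3).** The micronutrient outcome is "Changes in Vitamin D, iron, and calcium levels", with the justification "Provides insight into nutritional and bone health improvements". For liver enzymes and creatinine with eGFR, the justification is "Indicates improvements in organ function".
- **Analysis of secondary endpoints (12.4.3).** All laboratory measurements are listed among the secondary outcomes. The test is left to the type of variable, and effect sizes are adjusted odds ratios from mixed-effects models.
- **Safety analysis (12.4.4).** The whole of it is "Frequency and severity comparisons across groups in terms of AE and SAE reported and other details from documentation in safety reports".

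**The concern.** The protocol gives these tests a safety role when it collects them and an effectiveness role when it analyses them. The harms it lists for the supplements include several that a blood test can show before symptoms appear. If the safety results rest on what someone chooses to report, a symptom-free value above range may or may not be counted, and the two arms may differ in how readily it is reported.

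The outcome wording adds to this. Section 3.3 reads change in the supplemented nutrients, and in liver and kidney tests, as improvement. For a nutrient that is to be kept within a range, a rise is favourable below the range and unfavourable above it. A change score alone does not separate the two.

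At stake is whether the trial can show, from data it already holds, that the package did or did not push participants out of range on the harms it names.

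**Working it through.** The protocol states no figure on this point. It gives no calcium, iron or vitamin D distribution, no expected frequency of excursions, and no final number of participants or clusters. No arithmetic applies, so the check follows the tests through the document.

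**Step 1: where the tests enter and where they leave.**

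| Stage | Section | Role given to the tests |
|---|---|---|
| Named harm | 2.3.1 | Calcium (with 10.5 mg/dL), kidney, vitamin D, iron |
| Collected | 9.2 | Safety assessment, and also outcome |
| Defined | 3.3 | Change, justified as improvement |
| Analysed by name | 12.4.3 | Secondary endpoint |
| Safety analysis | 12.4.4 | Not named |
| Interim safety criterion | 12.4.7 | Not named; incidence and severity of adverse events only |

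The exploratory analyses in 12.4.10 do mention laboratory parameters, but only those that are not primary or secondary outcomes, so these tests fall outside them. Section 12.4.3 is therefore the only analysis that names them.

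**Step 2: direction.** Section 6.2 sets a target with a lower and an upper limit. Section 3.3 has no upper limit and no unfavourable direction for the same nutrients. The two sections describe the same measurements on different scales.

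**Step 3: other routes into the safety results.**

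- *Adverse event reports.* Section 10.1 covers any undesirable medical occurrence, which could include a laboratory value. Its elaboration mentions only new symptoms and worsening of existing conditions. No section says that an out-of-range value is to be recorded as an adverse event.
- *Events of special interest.* Section 10.8 could take in an excursion through its example of unexpected physiological changes. It gives no analyte and no limit, and hypercalcaemia is an anticipated risk under 2.3.1, so it need not qualify as unexpected.
- *Dose monitoring.* Section 6.2 means that someone looks at each value. Nothing says that a value which prompts a change is then counted by arm.
- *The closing clause of 12.4.4.* It reaches laboratory data only if a safety report has been filed that contains them.

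Each route makes capture possible. None makes it a requirement.

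**Step 4: cross-reference.** Section 9.2 points twice to section 3.2 for these tests. They are defined in 3.3; 3.2 holds the secondary objectives.

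**The case against.** Two stronger readings are tempting, and the documents do not support either.

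A reader might infer that the laboratory values are analysed only as means. Section 12.4.3 does not say so. It leaves the test open and names adjusted odds ratios, which imply some categorisation, although none is stated for laboratory values. An in-range or out-of-range split is not excluded.

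A reader might also infer that hypercalcaemia or iron overload would be missed, or reported as benefit. That is too strong. Besides the routes traced above, individual data are tabulated by measure and time point (12.4.9), a final analysis of risks and benefits is planned (2.3.3), and an independent board reviews safety data (13.7). Severity grading by tolerance and daily impact (9.2, 10.3) does not block capture either: a symptom-free excursion recorded as an adverse event could be graded mild and would still count towards frequency.

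It is also fair to say that shift tables and abnormality listings are ordinary content of a statistical analysis plan, which is not shown here. The laboratory forms, adverse event forms and manual of procedures listed in section 17 are not shown either, and may hold a rule on abnormal values. Their layout is no finding. Likewise, 10.5 mg/dL is a background remark about symptoms and not a trial threshold, and the improvement wording in 3.3 justifies an endpoint without binding its interpretation.

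What stands after this is narrower. The protocol declares a safety role for these tests, assigns them by name only to the effectiveness analysis, and has no sentence that carries out-of-range values into the safety results. A statistical analysis plan written from it would start from that assignment.

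**Conclusion.** The point holds as a mismatch between the declared safety role of these tests and the stated safety analysis. Capture of a symptom-free out-of-range value is possible but not assured. It is worth correcting because the harms concerned are ones the protocol names, and because counting measured values by arm is more objective than voluntary reporting.

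No numerical size is given. Any estimate of how far an arm mean would move, or how many participants would be affected, would rest wholly on assumed inputs. The conclusion assumes only that the visible protocol text governs. If an annex already requires out-of-range values to be recorded as adverse events, the gap narrows to naming that rule in 12.4.4.

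**What to change.** In 12.4.4, state that the safety analysis includes, by arm at 6 and 12 months, the number and percentage of participants with values outside the laboratory's reference limits, in both directions, for calcium, iron, vitamin D, ALT, AST, creatinine and eGFR. Count calcium also above the 10.5 mg/dL figure cited in 2.3.1, as a reporting level only.

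State whether such values count as adverse events or as events of special interest.

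Keep the change outcomes in 3.3. For the supplemented nutrients, add the proportion within the reference range as a further summary, in line with the target in 6.2.

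Correct the pointers in 9.2 from section 3.2 to 3.3.

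The cost is a few extra tables from tests already scheduled, with no new visit or sample. The counts are likely to be small and mainly descriptive. These are reporting rules; no dose or treatment rule is proposed.
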